## 2. Methods

### 2.1. Study Design

The ImPaCt study is a parallel group blocked randomized controlled trial (RCT) with nested feasibility in which the PCI plus usual assessment of client complexity will be compared to usual assessment method alone. Blocked randomization will ensure a balance in the number of participants between the study groups in the trial and the next participant group allocation is less predictable, reducing the risk of selection bias [42,43]. The data will follow the CONSORT guideline including the CONSORT checklist [43].

### 2.2. Setting and Participants

The PCI will be trialed in a regional Victorian community nursing service, Australia, located at Bendigo Health. The community nursing service is funded by the Australian CHSP to provide traditional district nursing care to clients residing within a radius of 30 km from the service center. Clients are eligible for the service if aged 65 years old and over, have physical and cognitive function limitations, require assistance to remain living independently at home and remain engaged in their community [18]. Approximately 60 newly referred clients are seen monthly in the service by a team of 34 nurses who work a two-shift roster per day for seven days. At any one time, there are over 500 clients using the service. Community-dwelling client are referred to the service from My Aged Care, hospitals, doctors, other health practitioners, family members or themselves. Common reasons for referral are personal care, medication management, wound care, dementia support, diabetes management or continence management. Upon receiving the referral, the Intake Nurse triages the referral, collates all available information, and assigns a nurse who will visit the client for initial face-to-face assessment. A predetermined amount of time is allocated to completing the initial assessment and the associated clinical care. However, the assessment nurse may adjust this time once the assessment has been completed, for subsequent visits, based on the nurse’s assessment of care needs and nurses’ clinical judgment of level client complexity. Even though the information collected in the assessment is comprehensive, interpretation of the information is inconsistent, unstandardized and largely subjective. The decision regarding client complexity is reliant on the skill and clinical judgment by nurses.

Newly referred client assessment will form the unit of evaluation in this study. Nurses who perform these assessments will also be included as participants over the period from 1 July 2019–30 September 2020.

### 2.3. Inclusion Criteria

The inclusion criteria are new referrals of clients aged 65 and over and meet the criteria for CHSP funded services as explained above. All Registered Nurses employed as District Nurses in the community nursing service and are allocated a new client assessment during the trial period will be included. Assessments will be those performed during weekdays.

### 2.4. Exclusion Criteria

Exclusions will be client referrals for specific episodic care such as anti-coagulant therapy or eye drops post-eye surgery. Nurse participation is voluntary therefore, assessments completed by a nurse who declines to participate in the study will not be considered.

### 2.5. Intervention

In this proposed study, the intervention will be made up of the PCI plus usual care assessment of complexity. The PCI measures complexity across six domains engagement in care planning, clinical need (physical and psychological), social contact, family and carers, resources, and safety. Items are scored on a Likert scale of 1 to 5 and are added to give a total score from 6 (low complexity) to 30 (high complexity). The PCI was developed in a community nursing service caring for adults in Wales and validated using Rasch analysis to determine the probability of an item indicating complexity. Each item in the PCI was determined to be a good fit to determine complexity.

### 2.6. Sample Size

Initial data will be used to conduct a post hoc sample size calculation. Up to *n* = 34 (all) nurses in the community nursing service will make up the nurse participant sample. These are nurses making up the team who would normally be available to conduct assessments on referred clients. Based on the number of new referrals expected over three-month period, a convenience sample of up to *n* = 180 patient assessments (90 per group) will be targeted and up to *n* = 27 (all) nurses in the service will make up the nurse participant sample. Due to the pilot nature of the study, formal sample size calculation is not critical. Pilot studies by their nature are not aimed at establishing a definitive effect, however a rationale for sample size basis such as described above is deemed sufficient [44,45].

Using our early pilot data, post hoc sample size calculation was performed based on the proportions of the level of complexity rating in the ImPaCt study. A minimum total sample *n* = 138 patient assessments, i.e., 69 per group (Figure 1) will be required in definitive trial to detect a significant difference in proportions relating to a high level of complexity rating between the control (23.1%) vs. intervention (5.7%), odds ratio = 4.97, power = 0.8 and *p* < 0.05.

### 2.7. Randomization

The study randomization schedule will be designed by an independent person who will not be implementing the study procedures. Randomization will occur at the level of the type of assessment (PCI plus usual assessment vs. usual assessment alone) using 45 blocks of 4 block sizes.

Allocations will be concealed in sequentially numbered, sealed opaque envelopes prepared by an independent person. An envelope will be sequentially drawn from a closed box and opened to reveal the assessment allocation, each time a new assessment needs to be performed. Once opened the allocation cannot be re-used if for whatever reason it is not used for that assessment.

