### 2.8. Study Procedures

Prior to participating in the study, nurses will be briefed about the project and provided with a brief education about using the PCI. This will ensure that each nurse receives the same information. No further instruction will be provided on the PCI which will remove the risk of researcher influence.

Each nurse will be allocated a code that will be used for each assessment they complete. This code will not identify the nurse and will be provided by an independent person, it will be used for analysis purposes only. The code will be allocated to each nurse involved using a sealed envelope system at the commencement of the project and on consent. This will ensure that data related to the learning effect can be analyzed.

The nurses will be provided with an introduction to the PCI and asked to complete the nurse pre RCT survey (File S1 in Supplementary). On completion of data collection, the nurse will be asked to complete the post RCT survey (File S2 in Supplementary).

As described earlier in local context, the Intake Nurse is responsible for allocating new referrals for assessment to nurses through a daily list. They will in addition provide the sealed group allocation envelope to the nurse on return to the office. On return, the nurse will open the envelope to determine the group type. The nurse will then retrieve the appropriate group envelope containing the required study documents. The control group envelope will contain the nurse information and consent (File S3 in Supplementary) and the nurse assessment survey 1 (File S4 in Supplementary). The intervention group envelope will include, in addition to the above, the PCI (File S5 in Supplementary) and the nurse assessment survey 2 (File S6 in Supplementary).

The control group: an assessment will be completed following the current usual process. The nurse conducting the assessment will be asked to rate and justify the client’s complexity using judgment as usual and will not be prompted in any way.

The intervention group: an assessment, documentation and data collection will be carried out as for the control group with exception of the inclusion of survey 2. Once client assessment has been completed and away from client interaction, the nurse then completes the PCI and nurse survey 2 which comprises of questions pertaining to the PCI. The researcher will not lead or prompt the nurses.

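### A constant block size of 4 makes about a third of allocations deducible for anyone who follows the sequence, and section 2.1 wrongly says blocking makes the next allocation less predictable

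*Protocol article*

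**What the plan says.** All references are to the protocol article.

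- **Block structure (2.7).** Randomisation is by type of assessment, "using 45 blocks of 4 block sizes". Section 2.6 gives the target: up to 180 "patient assessments (90 per group) will be targeted".
- **Rationale (2.1).** Blocking is said to balance the groups and to mean that "the next participant group allocation is less predictable, reducing the risk of selection bias".
- **Concealment (2.7).** "Allocations will be concealed in sequentially numbered, sealed opaque envelopes prepared by an independent person".
- **Handling (2.8).** "the Intake Nurse is responsible for allocating new referrals for assessment to nurses through a daily list". The same role hands over the envelopes: "They will in addition provide the sealed group allocation envelope to the nurse on return to the office". Then: "On return, the nurse will open the envelope to determine the group type", after which that nurse collects the pack for the arm.
- **Rating (2.8, 2.9).** In the control arm, "The nurse conducting the assessment will be asked to rate and justify the client’s complexity using judgment as usual". In the intervention arm the same nurse completes the PCI, which supplies the rating there.
- **Setting (2.2).** There is one community nursing service, and 2.7 describes a single run of envelopes.

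**The concern.** Blocking secures balance. It does so by constraining the sequence, and that constraint lets later allocations in a block be worked out from earlier ones. The smaller and more regular the block, the more can be worked out. The reason given in section 2.1 therefore points the wrong way, and it may have led the authors to think that a fixed block of 4 needed no further protection.

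The setting makes this worth attention. The trial has one sequence, the assessing nurse learns the arm on opening the envelope, and one role both assigns referrals and gives out envelopes. Sealing hides what an envelope contains, but not what can be inferred from those already opened. If someone did foresee an arm, they could influence which assessment takes the next envelope, and the comparability that randomisation should give would be weakened.

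**Working it through.** **Inputs.** 45 blocks and block size 4 (section 2.7); target 180, 90 per group, hence 2 + 2 in each block (section 2.6).

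**1. Is the block size constant?** 45 × 4 = 180, which is the stated target. It also equals three months at the roughly 60 new referrals a month given in section 2.2 (60 × 3 = 180). The wording could be misread as four different sizes, but that reading would not explain the exact match.

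**2. Allocations known with certainty.** A 2:2 block has six equally likely sequences: AABB, ABAB, ABBA, BAAB, BABA, BBAA. An allocation is determined once one arm is used up.

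| Position | Probability determined |
|---|---|
| 1 | 0 |
| 2 | 0 |
| 3 | 2/6 = 1/3 (AABB, BBAA) |
| 4 | 1 |

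The expected number per block is 1 + 1/3 = 4/3, so the share is (4/3)/4 = 1/3. Over 45 blocks that is 45 × 4/3 = 60 of 180. Each block contributes 1 (probability 2/3) or 2 (probability 1/3), with variance 2/9. The SD over 45 blocks is √(45 × 2/9) = √10 ≈ 3.2, and the possible range is 45 to 90.

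**3. Success of guessing the arm that is behind** (a coin toss when level):

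- Position 1: 1/2
- Position 2: 2/3
- Position 3: (2/3 × 1/2) + (1/3 × 1) = 2/3
- Position 4: 1

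The mean is (1/2 + 2/3 + 2/3 + 1)/4 = 17/24 = 70.8%. Under simple 1:1 randomisation nothing is determined and any guess is right 50% of the time. Fixed blocks of 4 thus raise predictability, contrary to section 2.1.

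**4. What other block schemes would give.** The fixed-size rows are exact enumeration. The varying rows come from 1,000 simulated schedules of 180, with an observer who knows the set of possible sizes but not the size of any given block.

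| Scheme | Known with certainty | Foreseeable with probability ≥ 80% | Best guess correct |
|---|---|---|---|
| Fixed 4 (plan) | 33.3% (60) | 33% | 70.8% |
| Fixed 6 | 25% (45) | – | 68.3% |
| Fixed 8 | 20% (36) | – | 66.6% |
| Varying 4, 6 | 5.4% (about 10) | 26% | 69.2% |
| Varying 4, 6, 8 | 2.2% (about 4) | 25% | 68.0% |

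Varying the size removes nearly all certainty, but it does little to the average guess.

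**The case against.** A reader might infer that staff will know a third of the allocations, that the Intake Nurse can steer clients or nurses between arms, and that the primary comparison is therefore biased. The documents do not support that.

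- **Three conditions must hold together.** The one-third figure applies to someone who knows the block size, sees every earlier result and sees them in order. The article does not say that staff are told the block size or that the Intake Nurse sees what each envelope held; the assessing nurse opens it. Nor does it say that one individual fills the intake role throughout. An assessing nurse who sees only her own envelopes, in a team of 27 to 34 (both figures appear in section 2.6), could not reconstruct the run.
- **Pairing precedes the envelope.** Under section 2.8 the referral is assigned through the daily list and the envelope is handed over only when the nurse returns. Client and nurse are already matched, so steering would also require anticipating or controlling the order in which returning nurses receive envelopes.
- **Unmasked rating is a separate matter.** The nurse knows the arm before completing the study forms whatever the block scheme. Varying the block size does not change that, nor does it stop an opened allocation from going unused.
- **The benefit is partial.** The best-guess rate moves only from about 71% to about 68%.

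All of this stands, and it limits how far the point reaches. Two things survive it. The statement in section 2.1 is wrong against simple randomisation, however the envelopes are handled. And the plan prints a fixed, small block size without saying that it is withheld from the staff who handle the sequence. The protection from late opening is also less firm than section 2.8 suggests, because section 2.7 has the envelope drawn and opened whenever a new assessment falls due, which could be before the visit.

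**Conclusion.** The point holds as one of avoidable predictability plus an incorrect rationale. With a constant block of 4, an expected 60 of 180 allocations are determined in advance and a lagging-arm guess succeeds 70.8% of the time, against none and 50% under simple randomisation. These figures rest on a 2:2 split in every block and on an observer who knows the block size and follows the whole sequence; whether anyone at the site would be in that position is not stated. The envelope procedure is a real safeguard. The documents do not show that allocation will be subverted or the primary result biased. The importance is modest, but the remedy is standard and nearly free, so it should be made.

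**What to change.** 1. Section 2.7: have the independent person generate the list in permuted blocks of randomly varying size (for example 4, 6 and 8), and state that the sizes are not disclosed to the Intake Nurse or the assessing nurses.
2. Section 2.1: say that blocking secures balance in numbers, and that undisclosed varying block sizes limit prediction of the next allocation.
3. Reconcile sections 2.7 and 2.8 on when the envelope is drawn and opened, so that one sequence of events is described.

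The cost is a new list and a slight imbalance between arms if the last block is incomplete. Recruitment dates in section 2.2 (from July 2019) and the use of early pilot data in section 2.6 suggest that the list may already be in use. In that case, apply the change to the remaining allocations or to the definitive trial that section 2.6 refers to, correct the rationale, and report the fixed block size as a limitation.

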### 2.8. Study Procedures

Prior to participating in the study, nurses will be briefed about the project and provided with a brief education about using the PCI. This will ensure that each nurse receives the same information. No further instruction will be provided on the PCI which will remove the risk of researcher influence.

Each nurse will be allocated a code that will be used for each assessment they complete. This code will not identify the nurse and will be provided by an independent person, it will be used for analysis purposes only. The code will be allocated to each nurse involved using a sealed envelope system at the commencement of the project and on consent. This will ensure that data related to the learning effect can be analyzed.

The nurses will be provided with an introduction to the PCI and asked to complete the nurse pre RCT survey (File S1 in Supplementary). On completion of data collection, the nurse will be asked to complete the post RCT survey (File S2 in Supplementary).

As described earlier in local context, the Intake Nurse is responsible for allocating new referrals for assessment to nurses through a daily list. They will in addition provide the sealed group allocation envelope to the nurse on return to the office. On return, the nurse will open the envelope to determine the group type. The nurse will then retrieve the appropriate group envelope containing the required study documents. The control group envelope will contain the nurse information and consent (File S3 in Supplementary) and the nurse assessment survey 1 (File S4 in Supplementary). The intervention group envelope will include, in addition to the above, the PCI (File S5 in Supplementary) and the nurse assessment survey 2 (File S6 in Supplementary).

The control group: an assessment will be completed following the current usual process. The nurse conducting the assessment will be asked to rate and justify the client’s complexity using judgment as usual and will not be prompted in any way.

The intervention group: an assessment, documentation and data collection will be carried out as for the control group with exception of the inclusion of survey 2. Once client assessment has been completed and away from client interaction, the nurse then completes the PCI and nurse survey 2 which comprises of questions pertaining to the PCI. The researcher will not lead or prompt the nurses.

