### 2.9. Outcomes

The primary outcome of the RCT component is client complexity rating (low, moderate, or high) as measured using the PCI (intervention) or usual assessment nurse judgment alone (control).

The first secondary outcome is the addition of nursing care interventions after initial assessment. These are the required interventions for the client based on the assessment outcome and the detected level of client complexity. The nursing care interventions will be categorized as medication support, wound care, referrals and liaison and others. The second secondary outcome is the nursing care time added in minutes. This is the additional time that may be allocated to the delivery of the nursing care interventions for the clients following assessment and detected level of client complexity. 

Data will be collected using baseline and follow up surveys (File S1 and S2 in Supplementary) completed by participating nurses allocated to the intervention group pre- and post-PCI use. The survey will be administered electronically or via paper form. It will be supplemented with field notes and observations recorded by the researcher throughout the study. Any focus groups or interviews conducted will be recorded for transcription.

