### 2.10. Data Analysis

Statistical analysis will be carried out in IBM SPSS Statistics Version 24 (IBM Corp, New York, NY, USA). For quantitative data analysis, statistical significance will be indicated by *p* < 0.05.

Participant characteristics and survey data will be analyzed and presented using summary descriptive statistics. Statistics will include mean and standard deviation for continuous data, median and interquartile range for ordinal data and percentage and 95% confidence interval for nominal data. Comparative univariate statistics will be conducted to test for differences between control and intervention characteristics. Parametric and or non-parametric statistical tests will be used to compare the groups.

Currently the PCI has no cut-offs for the level of complexity ratings. Preliminary data will be used in a receiver operating characteristics (ROC) analysis to determine complexity rating cut-offs (categorized as low, moderate, or high) with usual care complexity rating as the criterion. Categorial level of complexity rating as a primary outcome will be compared between control and intervention groups using the Chi-square independence test.

For the first secondary outcome, modification of nursing interventions (addition or subtraction of nursing interventions), between group comparisons will be performed on distribution of intervention categories. The second secondary outcome, clinical time will be compared between the study groups using ordinal regression. Clinical time as the dependent three level categorical variable. Age and nurse’ years of community experience will be covariates, while gender, reason for referral, group allocation (intervention or control) and level of complexity rating will be factors in the regression analysis.

Qualitative data collection will be from surveys, additional information regarding nursing interventions, nurse’s feedback, field notes and observations recorded by the researcher. Audio-recorded information from focus groups will be transcribed verbatim. Inductive thematic analysis has been chosen because this will ensure that themes emerge from the data (bottom-up approach). Analysis will be conducted using Braun and Clarke’s phases which include (1) data familiarization, (2) initial code generation, (3) theme search, (4) review of themes, (5) define and name themes [46].

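### The primary chi-square test treats ratings by the same 27 to 34 nurses, who work in both arms, as independent, and makes no use of the nurse code collected to study learning

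*Protocol article*

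**What the plan says.** - **Unit of randomisation (Section 2.7).** "Randomization will occur at the level of the type of assessment", with a fresh sealed envelope for each new assessment. Nothing ties a nurse to one arm.
- **Nurses (Sections 2.6 and 2.8).** All participating nurses are briefed and taught the PCI before they start. Section 2.6 gives their number once as up to 34 and once as up to 27, each time described as all nurses. Each nurse carries a code across assessments, and the stated reason is "This will ensure that data related to the learning effect can be analyzed".
- **Sample (Section 2.6).** For this study, "a convenience sample of up to *n* = 180 patient assessments (90 per group) will be targeted".
- **Primary analysis (Section 2.10).** The three-level complexity rating "will be compared between control and intervention groups using the Chi-square independence test", where "statistical significance will be indicated by *p* < 0.05". No term for nurse, order or earlier PCI use is named.
- **Clinical time (Section 2.10).** An ordinal regression includes nurses' years of community experience as a covariate but has no nurse term.
- **Surveys (Section 2.9).** Data come from surveys "completed by participating nurses allocated to the intervention group pre- and post-PCI use". The randomisation in Section 2.7 creates no such group of nurses.

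**The concern.** A chi-square independence test assumes that each rating is unrelated to every other. Here up to 180 ratings come from 27 to 34 people, about five to seven ratings each, on a judgement that Section 2.2 itself calls inconsistent and largely subjective. Ratings by one nurse are therefore likely to resemble each other.

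Separately, a nurse who has completed the PCI for one client may think differently about the next, including a control client. The protocol foresees a learning effect and collects the code needed to study it, but the test it fixes cannot use that code. At stake are the error rate and precision of the primary comparison, and whether a small or large group difference can be interpreted.

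**Working it through.** **1. The plan's own figure.** Section 2.6 states: "A minimum total sample *n* = 138 patient assessments, i.e., 69 per group (Figure 1) will be required in definitive trial", for "the control (23.1%) vs. intervention (5.7%), odds ratio = 4.97, power = 0.8 and *p* < 0.05".
- Odds ratio: (0.231/0.769) / (0.057/0.943) = 4.97, as stated.
- Two-sided Fisher exact power by full enumeration: 0.7945 at 68 per group and 0.8021 at 69. So 69 per group (138) is reproduced exactly, as a calculation on independent observations with no allowance for nurse or carry-over.
- The named test is a chi-square, so the power figures below use the pooled two-sided normal formula. At 23.1% vs 5.7% it gives 84% at 69 per arm and 92% at 90 per arm.

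**2. Ratings per nurse.** 180/34 = 5.3 and 180/27 = 6.7.

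**3. Effect of ignoring nurse on the primary test.** Simulated with 180 assessments in blocks of 4, nurses assigned at random, a true rate of 23.1% in both arms and a chi-square at 5%. The latent ICC values are assumptions.

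| Nurse's tendency | ICC 0.1 | ICC 0.3 |
|---|---|---|
| Same in both arms | about 5% | about 5% |
| Unrelated between arms | about 6% | 10 to 12% |

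The second row is an extreme, but a difference by arm is not far-fetched. Under Section 2.9 the control rating is unaided judgement and the intervention rating comes from the PCI, so one nurse's leanings on the two need not agree.

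**4. Control ratings made before a nurse's first PCI use.** Take a nurse with m assessments, each equally likely to fall in either arm. The expected number of control ratings before the first PCI use is 1 − 0.5^m, out of m/2 control ratings.
- 34 nurses: 0.975 / 2.65 = 0.37, or about 33 of 90 control ratings.
- 27 nurses: 0.990 / 3.33 = 0.30, or about 27 of 90.

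So 63 to 70% of control ratings are expected to follow the nurse's own use of the PCI.

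**5. Power if carry-over pulls control ratings toward PCI ratings.** Let c be the share of the 17.4-point gap (23.1 − 5.7) that an exposed control rating loses. The documents give no value for c, so a range is shown. The control rate becomes 0.231 − c × (0.63 to 0.70) × 0.174.

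| c (assumed) | Control rate | Power at 90 per arm |
|---|---|---|
| 0 | 23.1% | 92% |
| 10% | 22.0 to 21.9% | 89% |
| 25% | 20.4 to 20.1% | 84 to 83% |
| 50% | 17.6 to 17.0% | 71 to 67% |

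**6. Information available for modelling.** At the stated rates, 90 × 0.231 + 90 × 0.057 = 20.8 + 5.1, about 26 ratings of high in all. Among the 27 to 33 unexposed control ratings, 27 × 0.231 = 6 to 33 × 0.231 = 8 would be high.

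**The case against.** **Direction of carry-over.** A reader might infer that carry-over must shrink the effect. The documents do not support that. Section 2.10 says that the PCI has no cut-offs yet, so completing it gives a nurse no established threshold that would teach her to call fewer clients high. The trial's rationale is better detection, so exposed nurses might rate more control clients high, which would widen a 23.1% vs 5.7% gap. This stands: shrinkage is one plausible direction, not a finding.

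**The starting gap.** The two rates come from early data of this same study. If carry-over exists, the 17.4 points may already contain some of it, and step 5 would count it twice. This stands, so the power figures are illustrative.

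**Validity of the chi-square.** A reader might infer that the test is always too liberal. It is not: with a tendency shared across arms, error stays near 5%. Inflation needs tendencies that differ by arm.

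**The learning-effect analysis.** Section 2.8 says only that such data can be analysed. A supporting analysis may sit in an analysis plan that is not shown, so its absence here is not a broken promise. The named primary test is a different matter: the article fixes it, and it rests on independence that the design does not provide.

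**Pilot status.** Section 2.6 says that the study is not aimed at a definitive effect and ties 138 to a later trial. That lowers the stakes, but Section 1.5 states null hypotheses and Section 2.10 tests at 5%.

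**The time model.** Years of experience is an adjustment term, not a tested hypothesis, so an understated standard error for it changes no stated conclusion. The missing nurse term is a smaller matter there.

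**Conclusion.** The point holds in a limited form. The primary analysis is fixed as a test that ignores nurse although 27 to 34 nurses supply up to 180 ratings across both arms, and the nurse code has no role in any stated analysis.

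The consequence for the test ranges from a modest loss of precision to a true level of about 6% or 10 to 12%, depending on an unknown ICC and on whether nurses lean the same way in both arms. Carry-over has ample opportunity to occur, but its presence, direction and size are unknown. The fall in power to 89%, 83 to 84% or 67 to 71% applies only under the assumed 10%, 25% or 50% carry-over toward PCI ratings, and only if the pilot gap is undiluted.

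The survey wording in Section 2.9 conflicts with Sections 2.7 and 2.8. That is a separate, minor matter of reconciliation and does not affect the primary test.

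**What to change.** 1. In Section 2.10, replace the chi-square test by an ordinal (or, for high vs not high, logistic) model of rating on group, with a nurse random intercept or nurse-clustered standard errors. The clustered version also covers tendencies that differ by arm, which a shared intercept alone does not. With 27 to 34 nurses it needs a small-sample correction.
2. Add the nurse term to the clinical-time model.
3. Pre-specify a secondary analysis that adds the number of earlier PCI uses by that nurse and its interaction with group, and a sensitivity analysis limited to control ratings made before the nurse's first PCI use. State that the latter rests on about 27 to 33 control ratings and will be imprecise. State also that neither can restore an unexposed control, because every nurse is taught the PCI beforehand. With about 26 ratings of high, the interaction model is too heavy to be primary.
4. Reconcile the survey wording in Section 2.9 with Sections 2.7 and 2.8, and the two nurse numbers in Section 2.6.

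The cost is a change of wording, slightly more analysis work and possibly a wider interval. The nurse code is already recorded for every assessment and the envelopes are numbered in sequence, so no new data collection should be needed.
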